### Participants

#### Sample size and power calculation

Previous studies found effects of the Internet-based grief therapy of at least moderate size [46, 47]. Assuming moderate effect sizes, an alpha level of 0.05, and statistical power of 80% a target sample of 128 participants (64 for each group) is intended.

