### Statistical analysis

Demographic data and main outcomes will be reported using descriptive statistics. Chi-square and t-tests will be performed to examine whether randomization resulted in comparable groups and whether selective dropout occurred with regard to any pre-treatment characteristics.

To test the treatment effect, i.e. a significantly greater decrease in PGD and other mental health outcomes from baseline to post-treatment in the IG than in the WCG, a 2 × 2 repeated measure analyses of variance (ANOVA) will be conducted with time as the within-subject factor (baseline vs. post-treatment) and group as the between subject-factor (IG vs. WCG). Stability of treatment effects at 3, 6, and 12 month follow-up will be tested using two-tailed t-tests. Cohen’s d will be calculated to present effect sizes. Results will be shown for each outcome measure. Intention-to-treat analyses and completer analyses will be provided. Predictors of improvement in outcome measures and of dropout will be determined with linear and logistic regression analyses. To identify potential risk and protective factors for PGD severity and other bereavement outcomes as our secondary aim we will perform hierarchical regression analyses with baseline data, e.g., with religiousness, coping strategies, and attachment style as independent variables. All analyses will be conducted using SPSS, with an alpha level of 0.05.

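### The target of 128 is the complete-data minimum for 80% power at d = 0.5, so it holds no allowance for the dropout that the analysis section anticipates

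*Protocol article*

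**What the plan says.** The protocol article, under Sample size and power calculation, rests the design effect on earlier work: "Previous studies found effects of the Internet-based grief therapy of at least moderate size". It then gives the target: "Assuming moderate effect sizes, an alpha level of 0.05, and statistical power of 80% a target sample of 128 participants (64 for each group"). The section has no numeric effect size, SD, correlation, named test, sidedness or attrition rate. It does not say whether 128 counts participants randomised or participants analysed.

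Under Statistical analysis, the treatment-effect test is a 2 × 2 design: "repeated measure analyses of variance (ANOVA) will be conducted with time as the within-subject factor", with group as the between-subject factor. Alpha is repeated there: "All analyses will be conducted using SPSS, with an alpha level of 0.05". Only the follow-up comparisons are called two-tailed.

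The same section provides for dropout in three places: a check for selective dropout, separate intention-to-treat and completer analyses, and a regression: "Predictors of improvement in outcome measures and of dropout will be determined with linear and logistic regression analyses".

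Table 2 gives a retest reliability of 0.69 for the German ICG, taken from another source. It is the only figure in the article that bears on the correlation between baseline and post-treatment scores.

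**The concern.** The two sections do not fit together. One gives a target that reaches 80% power only if nobody is lost. The other plans three analyses around losing people. If 128 is the number randomised, any participant without a post-treatment ICG lowers the number that the power rests on. If 128 is the number of analysed participants wanted, the number to randomise is missing.

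The power of the planned time-by-group test also depends on rho whenever the effect is expressed in raw-score SD. A single 80% hides that dependence.

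What is at stake is how a non-significant primary result would be read. It would be judged against a stated 80% that the trial may or may not have.

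**Working it through.** **Inputs.** From the protocol: alpha 0.05, power 80%, 1:1 allocation, 64 per group, a moderate effect, and a 2 × 2 repeated-measures ANOVA. Assumed: moderate means d = 0.5; tests are two-sided; SDs at baseline and post-treatment are equal; attrition is equal in both arms at 10 to 35%; rho is 0.3 to 0.69.

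**Step 1: reproduce 128.** For a two-sample t-test with n per group, the noncentrality is d·√(n/2) on 2n − 2 degrees of freedom. At n = 64 and d = 0.5 it is 0.5 × √32 = 2.83 on 126 df, and power is 0.801. At n = 63, power is 0.795. The plan's figure is reproduced, and 64 is the minimum. A two-group F test with f = 0.25 and N = 128 also gives 0.801. Two other conventions do not give 64: a one-sided test needs 51 per group, and the repeated-measures interaction with f = 0.25 on the raw scale at rho = 0.5 needs 34 in total.

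**Step 2: the planned test.** The time-by-group interaction with two time points is a two-sample t-test on change scores. If d is in raw-score SD, then d_change = d / √(2(1 − rho)).
- At rho = 0.5, d_change = 0.5 / √1 = 0.5, so the result is again 64 per group.
- If d = 0.5 is already in change-score SD, the result is also 64 per group.

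The number therefore fits a post-score test and the planned test equally well.

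**Step 3: add attrition.** With n = 64 × (1 − loss) analysed per group, the power of the planned test at d = 0.5 in raw-score SD is:

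| rho | d_change | no loss | 10% | 20% | 30% |
|---|---|---|---|---|---|
| 0.3 | 0.423 | 0.660 | 0.614 | 0.563 | 0.507 |
| 0.4 | 0.456 | 0.727 | 0.680 | 0.628 | 0.570 |
| 0.5 | 0.500 | 0.801 | 0.758 | 0.707 | 0.648 |
| 0.6 | 0.559 | 0.881 | 0.845 | 0.800 | 0.744 |
| 0.69 | 0.635 | 0.946 | 0.922 | 0.889 | 0.844 |

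The rho = 0.5 row is also the power of a post-score t-test, and of the interaction with d in change-score SD. At rho = 0.69, power is still 0.816 at 35% loss.

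**Step 4: baseline-adjusted ANCOVA.** Here d_adj = d / √(1 − rho²). At rho = 0.5, d_adj = 0.5 / √0.75 = 0.577. With 25% loss, 64 × 0.75 = 48 per arm are analysed:

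| rho | ANCOVA, 48 per arm | ANOVA interaction, 48 per arm |
|---|---|---|
| 0.3 | 0.720 | 0.536 |
| 0.4 | 0.753 | 0.600 |
| 0.5 | 0.799 | 0.679 |
| 0.6 | 0.858 | 0.774 |

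Taking off one degree of freedom for the covariate changes these ANCOVA values by no more than 0.001.

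**The case against.** **The calculation was for the wrong test.** A reader might infer from the match with a simple t-test that the 80% belongs to a post-score comparison and was not computed for the planned ANOVA. The documents do not support this. No test is named, and Step 2 shows that the interaction gives the same 64 at rho = 0.5 or with d in change-score SD.

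**The planned ANOVA has lower power than stated.** This is not supported as a general statement either. At 20% loss its power is 0.80 at rho = 0.6 and 0.889 at rho = 0.69. The value 0.69 is a retest reliability from another sample. Selection on ICG of at least 25 and treatment effects that differ between people could make the trial's correlation lower, but nothing in the article shows that it is.

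**An allowance may be hidden in the number.** A one-sided test needs 51 per group, and 51 / 0.8 = 63.75, which also rounds up to 64. The article mentions neither a one-sided test nor an inflation. An ANOVA F test is not one-sided, and the only tests whose sidedness is stated are two-tailed. This reading is possible arithmetic without support in the text.

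**The design effect is conservative.** Earlier effects are described as at least moderate. At d = 0.6, the t-test still has 0.852 power at 20% loss and 0.802 at 30%. This is a fair point about the trial's likely prospects, but the 80% is claimed at the moderate effect and has to hold there.

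**The article is a condensation.** Test, correlation and missing-data method may stand in a fuller plan, so their absence is not a fault in itself. The point rests on the printed number, which is the zero-loss minimum at its plain inputs.

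**Conclusion.** The point holds in a limited form. On the plain reading of the stated inputs (d = 0.5, two-sided alpha 0.05), 128 is exactly the complete-data minimum and includes no allowance for the dropout that the analysis section anticipates.

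The size of the effect depends on quantities the article does not give. With d in change-score SD, or in raw-score SD with rho = 0.5, any loss takes the planned test below 80%: 76/71/65% at 10/20/30%. With rho below 0.5, it is below 80% before any loss. With rho of about 0.6 it breaks even at about 20% loss, and with higher rho it tolerates more.

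The flat 80% is therefore unverifiable for the planned analysis; it has not been shown to be wrong. A reader might add that keeping non-completers in an intention-to-treat analysis would dilute the effect further. No documented figure supports a size for that, and the earlier effects may already include non-completers.

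**What to change.** Keep 128 and rewrite the sample-size paragraph.

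1. State that 128 is the number randomised, and give the assumed attrition to T1.
2. Make the primary test an ANCOVA of T1 ICG adjusted for baseline ICG, which is already collected. At 20% loss and rho 0.3/0.5/0.6/0.69 its power is 0.747/0.825/0.879/0.933, against 0.563/0.707/0.800/0.889 for the ANOVA interaction.
3. Name the test, the effect scale and the sidedness, and give power over a range of correlations. Possible wording: 128 randomised; up to 25% without T1, leaving 48 per arm analysed; ANCOVA adjusted for baseline; two-sided alpha 0.05; d = 0.5 in raw-score SD; power 72/75/80/86% at an assumed T0–T1 correlation of 0.3/0.4/0.5/0.6.
4. If the repeated-measures ANOVA is kept, replace the flat 80% by its power over the same range of attrition and correlation. At 20% loss this is 56/63/71/80/89% at rho 0.3/0.4/0.5/0.6/0.69.

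The cost is one paragraph and, for the ANCOVA, a change to the named primary test. No further participants or measurements are needed. The 25% loss and the correlations are assumptions, and the paragraph should say so.

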#### Eligibility criteria

Participants are eligible for the study if they are 18 years or older, speak German, have Internet access and meet the diagnostic criteria for PGD after bereavement due to haematological cancer. Exclusion criteria are current psychotherapy or unstable psychopharmacological treatment with changes within the last 6 weeks, severe depression, suicide ideation, dissociative tendency, psychosis, PTSD due to an event other than the loss, substance use disorder, and cognitive or physical impairments which make treatment participation impossible.

### Intervention

Participants will receive therapist-assisted Internet-based grief therapy which applies the paradigm of structured writing. All therapeutic content, such as general information and writing instructions, is presented through a secure website (“Beranet”). Communication with the therapist is also conducted via an e-mail function of this website.

The Internet-based cognitive-behavioural grief therapy aims at working through the grief as well as coping with the new situation [46]. It is derived from a rationale developed by Lange et al. for individuals suffering from posttraumatic stress [35] which was adapted for PGD by Wagner et al. [46, 50, 51]. It is structured as a sequence of ten writing tasks in three phases: (1) self-confrontation, (2) cognitive restructuring, and (3) social sharing. The first phase focuses on loss-oriented coping, whereas phases two and three refer to restoration and integration of the loss experience [46].

Participants are instructed to plan out two writing tasks per week in advance, each lasting 45 min. They receive access to each writing task upon having completed the previous task. Once a week participants receive thorough feedback for their writing tasks from their therapist. All therapists are psychologists who were trained in the application of the intervention manual and receive supervision. Instructions for the writing tasks are mainly standardized and therapist instructions for individualized feedback are highly structured. Other than sending new writing tasks and feedback, therapists engage in further communication when directly contacted by the participant or when participants express critical experiences such as high distress or suicidal thoughts. In this case therapists address existing issues via mail or, if necessary, telephone. In case of endangerment of self or others, the participant’s general practitioner will be contacted to initiate immediate care for the participant.

Prior to the first phase, participants receive general information on the treatment, psychoeducation on the phases, and instructions on how to use the treatment platform. An overview of the Internet-based grief therapy and monitoring can be found in Table 1.

**Table 1 Tab1:** Intervention overview

Week	Phase	Procedure				
		Pre-Task- Monitoring		Task	Post-Task Monitoring	
1	Phase 1: Confrontation	SAM		Task 1	SAM	
		SAM	PHQ-9	Task 2	SAM	
		therapist feedback				
2		SAM		Task 3	SAM	
		SAM	PHQ-9	Task 4	SAM	WAI-S
		therapist feedback				
3	Phase 2: Cognitive reappraisal	SAM		Task 5	SAM	
		SAM	PHQ-9	Task 6	SAM	
		therapist feedback				
4		SAM		Task 7	SAM	
		SAM	PHQ-9	Task 8	SAM	WAI-S
		therapist feedback				
5	Phase 3: Social Sharing	SAM		Task 9	SAM	
		SAM	PHQ-9	Task 10	SAM	WAI-S
		therapist feedback				

*SAM*, Self-Assessment-Manikin; *PHQ-9*, Patient Health Questionnaire; *WAI-S*, Working Alliance Inventory

*Phase 1: Self-confrontation.* In four writing tasks participants describe their loss experience with a special emphasis on emotional and cognitive processes. They are instructed to write in as much detail as possible focusing on emotional and sensory perceptions, use present tense and first person, and not mind possible issues of style, grammar or orthography. The goal of this phase is to weaken feelings such as fear and guilt through reprocessing and therefore reduce avoidant behaviour.

*Phase 2: Cognitive reappraisal.* The next four writing tasks focus on a change of perspective to help participants develop realistic and helpful coping strategies. This is achieved by instructing participants to compose a supportive letter to a (possibly hypothetical) friend who endured the same kind of loss. The letter should reflect on and acknowledge burdensome feelings like guilt, fear, or anger, but also provide correction of unrealistic assumptions and dysfunctional thoughts. Participants are instructed to encourage their friend in activating resources, such as positive activities or social contacts as well as in finding rituals to express their mourning. The goal of this phase is to help participants define a new role for themselves and regain a sense of control over their lives.

*Phase 3: Social Sharing.* In the last two writing tasks participants are instructed to write a letter to a person concerned with the loss who can be also themselves or the deceased. The last letter serves as an opportunity to summarize and communicate what they may have learned during the therapeutic process and what they want to implement to cope with their loss experience.

New writing tasks are only released if the previous task has been completed. Participants can access past instructions, their texts and therapist feedback throughout the intervention and are encouraged to download all material for later rereading. Support for technical issues and issues regarding the intervention itself is provided via e-mail or telephone if necessary.

Before and after each writing task, participants complete a monitoring (Table 1) consisting of Self-Assessment-Manikin (SAM [52]), Patient Health Questionnaire (PHQ-9 [53]), and Working Alliance Inventory (WAI-S [54]).

### Measurements

The ICG [48] is used in its German version [55] to measure the primary outcome severity of PGD symptoms. It measures severity of PGD by assessing symptoms related to grief like yearning, intrusive thoughts, or resentment regarding the loss in 19 items which are rated by participants on a five-point Likert scale (never-always, 0–4) with regard to the last month. Three additional items were administered that are not included in the sum score but shall serve future comparability in the case of inclusion of PGD in ICD-11 as suggested by Maercker et al. [5]. They address feelings of guilt, difficulty accessing positive memories and anhedonia in questions adapted from Xiu et al. [56] as follows “I feel guilty about mistakes I made with regard to his/her death”, “It is really difficult for me to remember in detail happy moments with or images of him/her from the times before he/she died,” and “I no longer feel able to experience happiness, contentment, or joy since the loss of this person.”

Secondary outcomes, screening variables, moderators and mediators as well as used measures are summarized in Table 2.

**Table 2 Tab2:** Measurement tools

Construct	Instrument (abbreviation) [original and German source], additional information		Rating		Reliability	T-1	T0	Monitoring	T1-T4
		Item No.	Likert scale wording (scores)	Time frame					
Prolonged grief	Inventory of Complicated Grief (ICG) [48, 55], Cut-off^a^: ≥25 (sum score) [48]	19	never-always (0–4)	last month	*α*=.87, r_tt_ = .69 [55]	x	x		x
	Additional items [56], German version received from [name]	3	never-always (0–4)		–	x	x		x
	Prolonged Grief-13 – Interview version (IKT), [49, 61]	13	various formats (mostly 5-pointlLikert scales)	last month	–	x			
Depression	Patient Health Questionnaire (PHQ-9) [53, 62], Cut-off: ≥20 (sum, for severe depression) [63]	9	not at all-nearly every day (0–3)	last 2 weeks	*α*=.88 [64]	x	x	x	x
Posttraumatic stress	Impact of Event Scale-Revised (IES-R) [65, 66], Cut-off: > 0 (regression formula) [66], Screening: due to an event other than the loss, Baseline and post-assessments: due to loss	22	not at all-often (0,1,3,5)	last week	*α*=.71–.90, r_tt_ = .66–.80 [66]	x	x		x
Suicidal Ideation	Scale for Suicide Ideation (BSS or BSIS) [67, 68]	21	various formats (3 nuances each)	last week	*α*=.84–.89 [69]	x			
Psychosis	Dutch Screening Device for Psychotic Disorder (SDPD) [57], own translation from previous project, Cut-off: ≥13 (sum) [57]	8	not at all-completely true (1–5)	last 5 years	*α*=.68–.86 [57]	x			
Dissociation	Somatoform Dissociation Questionnaire (SDQ-5) [70, 71], Cut-off: ≥8 (sum) [70]	5	not applicable-highly applicable (1–5)	past year	*α*=.91, r_tt_ = .89 (long form) [71]	x			
Somatization	Patient Health Questionnaire (PHQ-15) [53, 62]	15	not bothered at all-bothered a lot (0–2)	last 4 weeks	*α*=.79 [64]		x		x
Anxiety	Generalized Anxiety Disorder Screener (GAD-7) [72, 73]	7	not at all-nearly every day (0–3)	last 2 weeks	*α*=.89 [73]		x		x
Health-related quality of life	Short-Form Health Survey (SF-12) [74, 75]	12	various formats	last 4 weeks	*α*=.57–.94 [75]		x		x
Sleep quality	Pittsburgh Sleep Quality Index (PSQI) [76, 77]	10	various formats	last 4 weeks	*α*=.85, r_tt_ = .87 [77]		x		x
Posttraumatic Growth	Posttraumatic Growth Inventory (PGI) [78, 79]	21	not at all-to a very great degree (0–5)	present	*α*=.92 [79]		x		x
Avoidance	Depressive and Anxious Avoidance in Prolonged Grief Questionnaire (DAAPGQ) [80], own translation	9	not at all true-completely true (0–7)	last month	*α*=.74–.90 [80]		x		x
Religiousness	Systems of Belief Inventory (SBI-15R) [81, 82]	15	completely true-not at all true (1–4)	present	*α*>.87 [82]		x		
Separation anxiety	Adult Separation Anxiety Questionnaire (ASA-27) [58], own translation	27	this has never happened-this happens very often (0–3)	lifetime	*α*=.95 [58]		x		
Attachment style	Relationships Questionnaire (RQ) [83, 84]	4	disagree strongly-agree strongly (1–7)	present/lifetime	–		x		
Quality of relationship to the deceased	Quality of Relationships Inventory (QRI) [85, 86] – adapted	25	not true-almost always true (1–4)	time before loss	*α*=.82–.89 [86]		x		
Childhood abuse and neglect	Childhood Trauma Questionnaire (CTQ) [87, 88]	28	never-very often (1–5)	childhood	*α*=.55–.89 [89]		x		
Circumstances surrounding the death, preparedness	Perception of circumstances surrounding the death and preparedness [59], own translation	4	various formats (7 nuances each)	time of loss	–		x		
Social support	Berlin Social Support Sales (BSSS) [90] (originally German), recipient version	32	strongly disagree-strongly agree (1–4)	present	*α*=.63–.83 [91]		x		x
Dependency	Depressive Experience Questionnaire (DEQ) dependency subscale [92, 93]	26	strongly disagree-strongly agree (1–7)	present	r_tt_ = .75 [93]		x		x
Self-esteem	Rosenberg self-esteem scale [94, 95]	10	not at all true-completely true (0–3)	present	*α*=.72–.85 [95]		x		x
Self-efficacy	Skala zur Allgemeinen Selbstwirksamkeitserwartung (Self-Efficacy Scale, SWE) [96] (originally German)	10	not at all true-completely true (1–4)	present	*α*=.80–.90 [96]		x		x
Coping strategies	Brief COPE [97, 98]	28	not at all-a lot (1–4)	lifetime	*α*=.61–.81 [98]		x		x
Stigma	Grief Experience Questionnaire (GEQ), subscale Stigmatization [60], own translation	10	never-almost always (1–5)	since loss	*α*=.86 (English version) [60]		x		x
Working alliance	Working Alliance Inventory Short Form (WAI-S) [54, 99] (only Monitoring and T1)	12	never-always (1–7)	intervention	*α*=.81–.91 [99]			x	x
Mood	Self-Assessment Manikin (SAM) [52]	3	(1–9)	present	–			x	

^a^Where a cut-off value is provided, it is used at T-1 to determine whether a participant fulfils eligibility criteria

Abbreviations: *α*=Chronbach’s alpha (internal consistency); r_tt_ = test-retest reliability

Published German translations of measurement tools are used where available. For all other measurement tools [57–60], own translations were achieved as follows: the first authors translated the measurement tools from English to German. A native English speaker retranslated the result, which was then checked for accordance with the original tool. Any inconsistencies and challenges in translating, e.g., idioms, were discussed thoroughly within the research team.

In addition to the variables listed in Table 2, sociodemographic variables, current medical problems, drug and alcohol consumption, history of previous losses, traumatic experiences, and of psychological problems, and help-seeking behaviour are assessed at baseline (T0).

All measures except the Prolonged Grief Interview [49, 61] are assessed by online self-assessment questionnaires which minimizes potential assessment bias.

### Statistical analysis

Demographic data and main outcomes will be reported using descriptive statistics. Chi-square and t-tests will be performed to examine whether randomization resulted in comparable groups and whether selective dropout occurred with regard to any pre-treatment characteristics.

To test the treatment effect, i.e. a significantly greater decrease in PGD and other mental health outcomes from baseline to post-treatment in the IG than in the WCG, a 2 × 2 repeated measure analyses of variance (ANOVA) will be conducted with time as the within-subject factor (baseline vs. post-treatment) and group as the between subject-factor (IG vs. WCG). Stability of treatment effects at 3, 6, and 12 month follow-up will be tested using two-tailed t-tests. Cohen’s d will be calculated to present effect sizes. Results will be shown for each outcome measure. Intention-to-treat analyses and completer analyses will be provided. Predictors of improvement in outcome measures and of dropout will be determined with linear and logistic regression analyses. To identify potential risk and protective factors for PGD severity and other bereavement outcomes as our secondary aim we will perform hierarchical regression analyses with baseline data, e.g., with religiousness, coping strategies, and attachment style as independent variables. All analyses will be conducted using SPSS, with an alpha level of 0.05.

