## Methods

The guided text-based intervention for people who suffer from PGD after bereavement due to haematological cancer is currently evaluated in a randomized waitlist-controlled trial. Questionnaires are administered at screening for eligibility (T-1), at baseline (T0), during the intervention (monitoring), at post-treatment (T1) and at three follow-up points (T2–4; 3, 6, and 12 months after intervention completion). Severity of PGD symptoms as measured with the Inventory of Complicated Grief (ICG) [48] is the main outcome. All questionnaires and the intervention are administered via a secure website and data is stored on secure storage devices. The procedure is described in detail below.

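### The primary test is an unadjusted change-score comparison; adjusting post-treatment ICG for baseline ICG would be at least as precise in large samples and costs nothing

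*Protocol article*

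**What the plan says.** The Methods section names the primary endpoint: "Severity of PGD symptoms as measured with the Inventory of Complicated Grief (ICG) [48] is the main outcome". The Statistical analysis section describes the effect to be tested as "a significantly greater decrease in PGD and other mental health outcomes from baseline to post-treatment in the IG than in the WCG", and fixes the test as a 2 × 2 model, in these words: "repeated measure analyses of variance (ANOVA) will be conducted with time as the within-subject factor (baseline vs. post-treatment) and group as the between subject-factor". The section names no baseline-adjusted model for the treatment effect.

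Under Sample size and power calculation, the article assumes moderate effects and an alpha of 0.05, and continues: "statistical power of 80% a target sample of 128 participants (64 for each group) is intended". It does not name the test behind that figure, the SD by which the effect is standardised, or a pre-post correlation.

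The ICG is completed at baseline (T0) before randomisation and again at T1 (Participant timeline; Table 2). Table 2 gives its test-retest reliability as .69 and an entry cut-off of 25 at screening.

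**The concern.** In a randomised trial with one baseline and one post-treatment value, the 2 × 2 interaction gives the baseline full weight: it subtracts T0 from T1 with a coefficient fixed at 1. ANCOVA estimates that coefficient from the data. When T0 and T1 are only moderately correlated, subtracting the whole baseline adds noise and over-corrects chance imbalance.

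Two things are at stake. Precision already paid for by collecting T0 ICG from everyone may be lost. And the stated 80% power may belong to a different test from the one planned, in which case it depends on a correlation that the article does not give.

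**Working it through.** **Inputs.** From the article: 64 per arm, alpha 0.05, 80% power, ICG test-retest .69. Assumed: moderate means d = 0.5; the test is two-sided (an ANOVA F-test is, and the follow-up t-tests are stated to be two-tailed); all 64 per arm are analysed. The pre-post correlation r is not given, so a range is shown.

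**Step 1: reproduce the plan's figure.** For a plain two-sample t-test, the noncentrality is d·√(n/2) = 0.5·√32 = 2.83 on 126 degrees of freedom. Power is 80.1% with 64 per arm and 79.5% with 63, so 128 is exactly the two-sample t-test figure. A within-between interaction calculation with f = 0.25 does not reproduce it: it gives totals of 46, 34 and 22 at r = 0.3, 0.5 and .69.

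**Step 2: what the planned test is.** With two time points, the interaction F-test equals the square of the t-test comparing T1 − T0 between groups.

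**Step 3: variances.** Let s0 and s1 be the SDs at T0 and T1.
- Change score: s0² + s1² − 2·r·s0·s1
- ANCOVA residual: s1²·(1 − r²)
- Difference: (s0 − r·s1)²

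The difference is never negative. It is zero when r·s1 = s0, that is, when the regression slope of T1 on T0 is 1. Example: s0 = 0.7, s1 = 1, r = 0.7 gives 0.51 for both.

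With s0 = s1 = 1 the variances are 2(1 − r) and 1 − r², with ratio 2/(1 + r). That is 2/1.5 = 1.33 at r = 0.5 and 2/1.69 = 1.18 at r = .69.

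**Step 4: power at 64 per arm.** With d on the raw-score SD and equal SDs, the effective d is 0.5/√(2(1 − r)) for the planned test and 0.5/√(1 − r²) for ANCOVA.

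| r | Planned test | ANCOVA |
|---|---|---|
| 0 | 51.0% | 80.1% |
| 0.3 | 66.0% | 83.7% |
| 0.4 | 72.7% | 86.5% |
| 0.5 | 80.1% | 90.0% |
| 0.6 | 88.1% | 93.9% |
| .69 | 94.6% | 97.2% |
| 0.8 | 99.3% | 99.7% |

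Simulation (20,000 runs each) agrees: 66.1% and 83.2% at r = 0.3, 79.6% and 89.6% at r = 0.5, 94.8% and 97.2% at r = .69. The planned test reaches 80% at r = 0.498. ANCOVA stays at about 80% or above throughout.

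**Step 5: sensitivity of the 0.5 threshold.** In general, the change score matches a T1-only t-test at r = s0/(2·s1). With s0 = 0.8·s1 the threshold is therefore about 0.4. If 20% were lost in each arm (an assumption) and SDs were equal, it would rise to 0.60. If d were defined on the change-score SD, the planned test would have 80% power at any r.

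**Step 6: the entry cut-off.** Selection on screening ICG can lower the T0–T1 correlation. Assume a trivariate normal model with all pairwise correlations .69. Cuts at −1, −0.5, 0 and +0.5 SD then give T0–T1 correlations of .62, .59, .56 and .52. With d = 0.5 on the truncated SD, the planned test has 90%, 87%, 85% and 82% power.

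**The case against.** The strongest defence is that nothing here is a wrong test. The article defines the effect as a difference in change, and the interaction tests exactly that. Under randomisation it is unbiased and controls the type I error. This stands: the point concerns efficiency only.

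A reader might go further in three ways that the documents do not support.
- **That the planned test is always less precise.** It is not: precision is equal when the slope of T1 on T0 is 1, and the article gives no SDs from which to rule that out.
- **That the trial has less than 80% power.** This needs r below about 0.5, equal SDs, d on the raw scale and complete data, and the article states none of these. Its only related figure, .69, puts the planned test near 95%. Allowing for the entry cut-off in the model of Step 6 still leaves it above 80%. The values r = 0.3 and 0.4 have no source in the article. On the other side, test-retest reliability is not the pre-post correlation in a trial with treatment in between, so .69 does not guarantee adequate power either.
- **That baseline significance tests will decide on adjustment.** The section says only: "Chi-square and t-tests will be performed to examine whether randomization resulted in comparable groups". It attaches no analysis decision to the result.

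It can also be said that model detail belongs in an analysis plan that is not shown. That does not remove the point, because the article itself fixes the test.

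**Conclusion.** The point holds as a matter of efficiency. The planned interaction test is valid, but in large samples it cannot beat baseline-adjusted ANCOVA and will usually lose to it. With equal SDs its variance is 33% larger at r = 0.5 and 18% larger at r = .69. At the article's only related figure the gain in power is modest, about 95% to 97%; at r = 0.5 it is 80% to 90%.

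The target of 128 matches a plain two-sample t-test at d = 0.5, not a calculation found for the planned interaction. Under raw-scale d, equal SDs and complete data, the planned test delivers the stated 80% only if r is at least about 0.5, whereas ANCOVA delivers about 80% or more whatever r is. A shortfall is therefore possible, not demonstrated.

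**What to change.** In the Statistical analysis section, make the primary analysis an ANCOVA of T1 ICG on group with T0 ICG as covariate, using the T1.0 assessment for the wait-list group. The equivalent mixed model with a common baseline mean would also do. Use the same model for each secondary outcome, with that outcome's own T0 value as covariate; Table 2 shows that these outcomes are measured at both T0 and T1.

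The cost is a few reworded sentences. The data and the software stay the same, and no participants are added. Under the conditions given in the verdict, the target of 128 then supports the stated power without relying on an unstated correlation.
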